## Abstract

**Background:**

Cardiovascular morbidity and mortality is increased in individuals with severe mental illnesses.

We set out to establish a multicentre, two arm, parallel cluster randomized controlled trial (RCT) of a health promotion intervention (HPI), IMPACT Therapy. The patient-tailored IMPACT Therapy aims to target one or more health behaviours from a pre-defined list that includes cannabis use; alcohol use; other substance use; cigarette smoking; exercise; diet and diabetic control, prioritising those identified as problematic by the patient, taking a motivational interviewing and CBT approach.

**Methods:**

Impact therapy will be delivered by care coordinators in the community to the treatment group and will be compared to treatment as usual (TAU). The main hypothesis is that the addition of IMPACT Therapy (HPI) to TAU will be more effective than TAU alone in improving patients’ quality of life as measured by the Short Form-36, including mental health and physical health subscales on completion of the intervention at 12 months post randomisation. A subsidiary hypothesis will be that addition of IMPACT Therapy (HPI) will be more cost-effective than TAU alone in improving health in people with SMI 12 months from baseline. The IMPACT therapy patient groups’ improvement in quality of life, as well as its cost effectiveness, is hypothesised to be maintained at 15 months. Outcomes will be analyzed on an intention-to-treat (ITT) basis.

**Discussion:**

The results of the trial will provide information about the effectiveness of the IMPACT therapy programme in supporting community mental health teams to address physical comorbidity in severe mental illness.

**Trial registration:**

ISRCTN58667926.

## Background

People with severe mental illnesses (SMI) such as schizophrenia, schizoaffective disorder and bipolar affective disorder die up to 20–25 years earlier than the general population[1-4]. Most of this premature mortality is due to physical disorders [5,6] with cardiovasular disease [7-9] and specially prominent. Worryingly, the mortality gap between those with schizophrenia and the general population appears to have widened in recent years [10].

High rates of modifiable cardiovascular disease (CVD) risk factors are seen in SMI, [11,12] including abdominal obesity; insulin resistance/glucose intolerance; hypertension; and dyslipidaemia;[13] these factors increase the chance of developing complications such as diabetes, heart disease, stroke, amputation, renal failure, blindness and ultimately, early death [14-17]. Antipsychotic medications accelerate weight gain and the onset of diabetes.[18-21]Once CVD risk factors develop, impaired motivation in SMI makes implementing lifestyle change challenging, [22,23] again increasing the risk of complications. On top of that, episodes of acute psychosis may interrupt diabetic control.

It is possible to prevent the development of CVD risk factors in SMI [24] and strategies exist to manage existing CVD risk [25]. The CATIE study confirmed that smoking cessation, nutrition counselling and supervised exercise programmes can help to reduce cardiovascular mortality in SMI [26], but this can be difficult to institute in practice. The UK government now emphasises the importance of health promotion in reducing cardiovascular disease burden in SMI [27,28]. However,no health promotion programmes have yet been adequately demonstrated in the UK to be reliable, reproducible and workable across the National Health Service (NHS).

To complicate matters, more people with SMI smoke cigarettes, [29,30] and use cannabis and other illicit drugs than do the general population [31,32]. On-going cannabis use leads both to poorer mental and physical health outcomes [33-37] with cannabis users on psychiatric intensive care units having higher serum glucose levels and heavier weights compared to non-cannabis users [38]. More recently developed treatment programmes for people with both psychosis and substance use show some promise [39-41] but are lengthy, complex and expensive. In clinical practice of course, parallel attendance at separate treatment programmes for physical health and drug use is often impractical.

A more practical alternative to separately addressing physical health and substance use may be an intervention targeting both lifestyle and substance use to maximize physical and mental health. We have developed a modular, manualised, health promotion intervention, IMPACT therapy [42], covering physical health, mental health and substance use, integrating the combined benefits of motivational interviewing and cognitive behavioural therapy (CBT) approaches at both individual and group level to effect lifestyle change. [42] This paper describes the study protocol for the Improving physical health and reducing substance use in Psychosis (IMPACT) randomised controlled trial (IMPACT RCT) to assess the effectiveness of IMPACT therapy (i.e. health promotion intervention (HPI)).

### Objectives

The primary objective is to determine the effectiveness and cost-effectiveness of the addition of an intensive health promotion intervention (IMPACT Therapy), designed to improve physical health and reduce substance use, to usual mental health care delivered by care coordinators (TAU) in people with severe mental illness (SMI) (defined as schizophrenia (ICD-10 code: F20), delusional Disorder (F22.0), schizoaffective disorder (F25), bipolar affective disorder (F31), recurrent depressive disorder (F32), current episode severe with psychotic symptoms (F33.3)).

The main hypothesis is that the addition of IMPACT Therapy (HPI) to TAU will be more effective than TAU alone in improving patients’ quality of life as measured by the Short Form-36, including mental health and physical health subscales [43] on completion of the intervention at 12 months post randomisation. This 12 month period incorporates an initial 3 months post randomisation to train the care coordinators to provide the IMPACT Therapy (HPI) over the following 9 months. We also hypothesise that the effect will be sustained three months after the end of the intervention, at 15 month follow up.

Our secondary hypothesis is that the addition of IMPACT Therapy (HPI) will be more cost-effective than TAU alone in improving health in people with SMI 12 months from baseline and that this cost-effectiveness will be sustained 3 months later at 15-month follow-up.

Subsidiary Hypotheses include

1. TAU plus IMPACT Therapy will reduce waist circumference by at least 1 cm at one year, compared to TAU alone

2. TAU plus IMPACT Therapy will be more effective in reducing weight at one year, compared to TAU alone

3. TAU plus IMPACT Therapy will result in a 50% reduction in proportion of people using cannabis compared to TAU alone.

4. TAU plus IMPACT Therapy will be more effective in reducing symptoms of psychosis compared to TAU alone

## Methods

### Design

A multicentre, two arm, parallel cluster randomized controlled trial (RCT) of an health promotion intervention, (HPI) IMPACT Therapy. The study was planned and implemented in concordance with the Consolidated Standards of Reporting Trials (CONSORT) cluster trial extension standards [44,45] to compare the cost-effectiveness of combining treatment as usual (TAU) plus IMPACT Therapy, versus TAU alone in improving health at one-year follow-up. Figure 1 summarises the trial design.

**Figure 1 F1:**
[figure not shown]
Summary of Trial design for Improving Physical health and reducing substance use in Psychosis – Randomised Control Trial (IMPACT RCT): Study protocol.

### Setting

The study will take place within community mental health teams (CMHTs), including continuing care/recovery teams; community rehabilitation; assertive outreach and community forensic teams in six Mental Health NHS Trusts in the urban and rural locations of South London, Sussex, Somerset, Staffordshire and Shropshire. We will not recruit from specialist first episode psychosis teams.

### Participants

Care coordinators permanently employed and intending to remain so for a period of one year within the CMHT settings above, with a minimum of four patients on their caseload with a primary diagnosis of SMI, are eligible for recruitment to the trial.

Patients of participating care co-ordinators are eligible for inclusion in the study if:

a) Aged between 18–65 years old.

b) A diagnosis of a psychotic disorder (ICD 10 diagnosis F20-29, F31.2, F31.5,)

Exclusion criteria:

a) A primary diagnosis of learning disability.

b) A co-existing physical health problem that would, in the opinion of the medical investigators, independently impact on metabolic measures and/or substance use habits.

c) Current pregnancy, plus mothers less than 6 months post-partum.

d) Life threatening or terminal medical conditions where intensive care is already provided.

### Pre-randomisation

All care-coordinators in participating CMHTs will be offered best practice treatment as usual training on physical health awareness, including the provision of health promotion leaflets on healthy dietary routines and physical exercise, together with information on general and community support for a healthy lifestyle. The purpose of this is to ensure that all care-coordinators, irrespective of which treatment arm they are allocated to, have the same baseline level of understanding of physical health issues, thus ensuring more standardised treatment as usual.

### Selection and randomisation

This is a cluster randomised trial and the randomisation will take place at the level of the care co-ordinator. To select the order in which first care co-ordinators and then patients are approached, a random numbers generator will be used. Researchers will approach each eligible care coordinator in this order and seek consent to participate in the trial, working down the list until the target sample size is achieved.

Prior to randomisation, consenting care-coordinators will provide a list of their current patient caseload. Patients on that caseload meeting the inclusion criteria will be entered into the random numbers generator to create a randomly ordered list in which to approach potential participants. Researchers will then approach these patients sequentially and seek informed consent to participate in the RCT. In situations where a patient does not wish to take part in the study, the researcher will select another patient from the list in that random order.

After completing baseline assessments on all consenting patients in a care co-ordinator’s caseload, the clinical trials unit will conduct randomisation of the care coordinators, stratified by borough, using randomisation blocks of random sizes to either treatment arm (IMPACT Therapy) or treatment as usual (TAU).

Researchers and the statistician will remain blind to treatment allocation. Outcome assessments will only be conducted by researchers blind to the treatment arm. Any violations of the study protocol will be recorded and reported to the Trial Steering Committee and the Data Monitoring and Ethics Committee.

### Intervention: IMPACT therapy

All consenting community care coordinators randomised to the IMPACT Therapy arm will receive 4-day IMPACT training on physical health and substance use in SMI, as well as training in motivational interviewing (MI), cognitive behavioural therapy (CBT) techniques and in running groups to deliver health promotion. The patient-tailored IMPACT Therapy aims to target one or more health behaviours from a pre-defined list that includes cannabis use; alcohol use; other substance use; cigarette smoking; exercise; diet and diabetic control, prioritising those identified as problematic by the patient, taking a MI and CBT approach. Participants may start the community-based IMPACT Therapy as soon as they are well enough to attend, even if they are in-patients, to mirror clinical practice. IMPACT Therapy is supported by a manual, a reference book and a service user handbook [46]. Each care coordinator in the active intervention arm of the study will receive copies of these books.

Care Coordinators allocated to the IMPACT Therapy arm of the trial will also receive supervision every 2 weeks to ensure fidelity of the intervention and to provide ongoing support and training. The supervision will be provided by research therapists by face-to-face contact, via video link or via Skype, supplemented by e-mail and/or telephone support.

Patients participating in the IMPACT therapy arm will have the option to receive three-monthly newsletters throughout the trial period (total of 4), each providing tips on healthy living. The information contained in the newsletter will comprise standard information that is readily available to the public.

### Outcome measures

Outcomes will be measured by self-report, objective assessments and face-to-face interviews. All participants will be assessed at the following time points: baseline (T0), 12 months post-randomisation (T1-at completion of intervention) and at 3 months after the end of treatment (15 months post-randomisation) (T2-) (Table 1). At each time point participants will be asked to repeat all baseline questionnaires plus provide a fasting blood sample and anthropometric measurements. 12- and 15-month follow-up windows will be defined as minus 6 weeks and plus 4 weeks for 12 month, and plus 4 weeks for 15 month follow-up. Data collected outside these time windows will be recorded but not used for the main analyses.

**Table 1 T1:** IMPACT outcome measures at defined timepoints

**Measure**	**Baseline**	**12 months**	**15 months**
SF-36 (Physical and mental health components)	X	X	X
Time line follow back	X	X	X
Nicotine dependence questionnaire	X	X	X
AUDIT	X	X	X
DINE	X	X	X
IPAQ	X	X	X
Waist/hip circumference ratio	X	X	X
BMI	X	X	X
Blood pressure	X	X	X
Fasting glucose	X	X	X
Insulin resistance	X	X	X
Long term blood glucose control (HbA1c)	X	X	X
Lipids	X	X	X
Uric acid	X	X	X
High sensitivity C reactive protein	X	X	X
Urine drug screen	X	X	X
PANSS	X	X	X
GAF	X	X	X
MADRS	X	X	X
OPCRIT	X	X	X
LUNSERS	X	X	X
Age at randomisation	X	X	X
Gender	X	X	X
Ethnicity	X	X	X
Marital status	X	X	X
Current medications	X	X	X
Medical history	X	X	X
Measures of compliance (1–7 scale)	X	X	X

Variables measured at baseline, 12 months and 15 months follow-up.

Baseline measures:

i. Sociodemographic data; age, gender, self-reported ethnicity, marital status.

ii. Quality of life: Short Form-36; including mental health and physical health subscales [43].

iii. Substance use measures: Time Line Follow Back; [47] Nicotine Dependence Questionnaire; [48,49]Alcohol Use Disorders Identification Test (AUDIT); [50] and a urine drug screen.

iv. Biomedical status measures: waist and hip circumference; height and weight to calculate body mass index; blood pressure; fasting blood glucose; insulin (to calculate the homeostasis model assessment-estimated insulin resistance (HOMA-IR) index); long term blood glucose control (as measured by glycated haemoglobin); fasting lipids; renal and liver function tests and other markers of cardiovascular risk and inflammation.

v. Lifestyles measures: adapted Dietary Instrument for Nutrition Education DINE; [51] adapted International Physical Activity Questionnaire (IPAQ) [52].

vi. Mental health status: Positive And Negative Syndrome Scale (PANSS)[53], Global Assessment of Functioning (GAF)[54], Montgomery Asberg Depression Rating Scale (MADRS) [55].

vii. Diagnosis; OPCRIT (Operational Criteria checklist) [56].

viii. Health care: Medical history of diabetes, cardiovascular disease and cerebrovascular disease; other past medical history. Family history of diabetes and related disorders.

ix. Current medications; Composite measure of compliance scale [57]; Liverpool University Neuroleptic Side Effect Rating Scale (LUNSERS) [58].

x. Costs: adapted Client Services Receipt Inventory (CSRI) [59].

xi. IMPACT Therapy dosage measures: HPI inputs and Supervision log form.

### Sample size

The power analysis is performed for the two subscales measures, Physical and Mental health components of SF-36 Quality of Life scale.[43] We have assumed a common standard deviation of the change scores between baseline and 12 month follow-up of 10 for the Physical component score and 12 for the Mental health component score (based on the QUATRO study [60]), supplemented with further information sought directly from the study team (project reference: QLG4-CT-2001-01734, European Union)) and a cluster size of 4 patients per care coordinator with intraclass correlation of 0.05. Using 80% power, a 5% alpha level and two-tailed assumptions, a sample size of 56 care coordinators and 216 patients are needed to detect a clinical significant difference of 5 points in Mental Health Component change score (Cohen’s d = 0.42), between two groups and a sample size of 38 care coordinators and 152 patients are needed to detect a clinical significant difference of 5 points in Physical Component change score (Cohen’s d = 0.5) between two groups. Assuming a drop-out rate of 20% of the care-coordinators and their patients and an additional patient drop-out rate of 30%, a total sample size of 98 care coordinators and 392 participants are needed for the Mental health score and 70 care coordinators and 280 participants for the Physical health score.

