### Intention-to-treat sample

The analysis will be performed on the basis of the intention-to-treat principle and will utilise all available follow-up data from all randomised participants. Follow-up data will be collected for all patients whose care-coordinator was randomized independent of whether a care coordinator dropped out or not.

The main statistical analyses will be targeted at estimating the difference in the mean outcomes of Physical and Mental health components of SF36 [43] at 12 and 15 months follow-up observation time point between treatment and control group using a mixed effects model. [63]The outcome variables are assumed to arise from normal distributions. This will be checked and if found to be lacking then appropriate transformations will be applied.

In the linear mixed effects model Physical and Mental health Component scores respectively, at 12 months and 15 months constitute the dependent variables. “Treatment randomisation group, “time (with two levels, 12 and 15 months post-randomization)”, the interaction between “treatment group and time”, “Borough”, and the “baseline values of Physical and Mental Health scores” are the fixed part of the model. “Care coordinator” will be included as a random factor in the model to account for the dependency of the observations within a cluster. “Time” will be entered as a categorical variable.

It is possible that the treatment effects will vary across the care coordinators delivering the interventions. We will therefore also assess an “intervention group x care coordinator” interaction term. A likelihood ratio test of the corresponding variance component and information criteria comparisons will be used to assess if the interactions should be included in the model. Similarly, the interaction between treatment and time will be assessed. Should there be evidence for such an interaction then the relevant terms will be kept in the model. For the final model, the group difference estimates and associated confidence intervals will be reported for 12 and 15 months after randomization.

No *a priori* subgroups were defined in the protocol.

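### One main hypothesis rests on two SF-36 component scores, each sized at an unsplit two-sided 5%, and the article does not say whether one or both must succeed

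*Protocol article*

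**What the plan says.** - **Objectives.** There is one main hypothesis: adding the therapy to usual care will do better in "improving patients’ quality of life as measured by the Short Form-36, including mental health and physical health subscales", at 12 months after randomisation. That the effect lasts to 15 months is stated as a further hypothesis. The Abstract separates the two in the same way.
- **Sample size.** "The power analysis is performed for the two subscales measures, Physical and Mental health components of SF-36 Quality of Life scale". One clause covers both calculations: "Using 80% power, a 5% alpha level and two-tailed assumptions". The standard deviations of change are "10 for the Physical component score and 12 for the Mental health component score", with "a cluster size of 4 patients per care coordinator with intraclass correlation of 0.05". The result is 216 patients for the mental component and 152 for the physical, or 392 and 280 after drop-out.
- **Intention-to-treat sample.** The main analysis estimates the group difference in the "Physical and Mental health components of SF36" at 12 and 15 months. Each score has its own mixed model, with estimates and confidence intervals reported at both times. No test level is given here.
- **Discussion.** Primary and secondary outcomes are listed together in one sentence. Quality of life is described there as covering both physical and mental health, which names the components but sets no rule for success.

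The article does not rank the components, does not say whether one or both must be positive, and mentions no multiplicity adjustment.

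**The concern.** A single claim can be carried by either of two tests. The significance level and power attached to that claim depend on how the two results are combined, and the article leaves this open after it has already fixed alpha, power and sample size. With no rule, a result on one component alone could be presented as support for the main hypothesis once the data are known. The 5% in the Sample size section would then be the level of each test and not of the claim. If both components were required, the 80% on each line would be the power for one component and not for the claim.

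**Working it through.** **1. Was 5% used in full for each component?**

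Inputs from the Sample size section: difference 5 points, SD 12 (mental) and 10 (physical), 80% power, clusters of 4, intraclass correlation 0.05. Design effect = 1 + (4 − 1) × 0.05 = 1.15. Patients per arm before clustering = 2 × (z for alpha + 0.842)² × SD² / 5².

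| Component | Two-sided alpha | Per arm | × 1.15 | Clusters per arm | Patients | Stated |
|---|---|---|---|---|---|---|
| Mental | 5% | 91 | 104.65 | 27 | 216 | 216 |
| Physical | 5% | 63 | 72.45 | 19 | 152 | 152 |
| Mental | 2.5% | 110 | 126.5 | 32 | 256 | – |
| Physical | 2.5% | 77 | 88.55 | 23 | 184 | – |

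Drop-out, rounding up to an even number of coordinators at each step:
- Mental: 54 / 0.8 → 68, 68 / 0.7 → 98, and 98 × 4 = 392.
- Physical: 38 / 0.8 → 48, 48 / 0.7 → 70, and 70 × 4 = 280.

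Both totals match the article, so the sizing used an unsplit 5% for each component. (The stated 56 coordinators for the mental component would give 56 × 4 = 224 patients; 216 patients and the total of 98 coordinators both correspond to 54.)

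**2. Error rate if either component suffices**

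With uncorrelated test statistics, 1 − 0.95² = 9.75%. The article gives no correlation between the components, so a range is assumed (bivariate normal):

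| Correlation | Two-sided error | False benefit only |
|---|---|---|
| 0 | 9.75% | 4.94% |
| 0.3 | 9.51% | 4.76% |
| 0.5 | 9.07% | 4.54% |
| 0.7 | 8.35% | 4.17% |
| 0.9 | 7.04% | 3.52% |

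The last column counts only errors in favour of the therapy: 1 − 0.975² = 4.94% at correlation 0, against 2.5% for a single test.

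**3. Error rate and power if both are required**

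Error is at most 5%. For power, take 392 recruited and 0.8 × 0.7 = 56% retained, which leaves 219.5 patients at 4 × 0.7 = 2.8 per coordinator. Design effect = 1 + 1.8 × 0.05 = 1.09, and the effective number per arm is 219.5 / 2 / 1.09 = 100.7.

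- Mental: expected z = (5/12) × √(100.7/2) = 2.957. Power is 84.1% at 5% and 76.3% at 2.5%.
- Physical: expected z = (5/10) × √(100.7/2) = 3.548. Power is 94.4% at 5% and 90.4% at 2.5%.
- Joint power at 5% each: 0.841 × 0.944 = 79% at correlation 0, 80.0% at 0.2 and 80.4% at 0.3.

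With exactly 216 analysed in clusters of 4, power is about 81% and 93%, so about 0.81 × 0.93 ≈ 76% jointly if independent.

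**4. Power under Holm at 392 recruited**

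A component succeeds if significant at 2.5%, or at 5% once the other has succeeded at 2.5%. With independent components and both effects real:
- Mental: 0.763 + (0.841 − 0.763) × 0.904 ≈ 83%.
- Physical: 0.904 + (0.944 − 0.904) × 0.763 ≈ 93%.

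If the physical component has no effect, the mental component has 0.763 + (0.841 − 0.763) × 0.025 ≈ 76%.

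**The case against.** The strongest reply is that a journal article condenses a fuller protocol and that multiplicity is usually settled in a statistical analysis plan, which is not shown. That stands as far as the choice of method goes, and the full documents may already contain a rule. It does not remove the point, because the article itself commits alpha, power and patient numbers, and what these mean for the main hypothesis depends on the missing rule.

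Three stronger readings are tempting, and the documents do not support them.

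- **That the trial's real error rate is almost 10%.** This needs a rule that either component suffices, which the article does not state, and uncorrelated components; 9.75% is the ceiling. It also counts false harm, whereas the main hypothesis concerns benefit. The article never calls 5% a study-wide rate, and the analysis section sets no test level, so testing each component at 5% is inferred from the sizing.
- **That the 15-month results are further routes to success.** Four independent tests would give 1 − 0.95⁴ = 18.5%, but the Abstract and Objectives place the main hypothesis at 12 months and treat 15 months as a separate sustained-effect hypothesis. Putting both times in one model does not change that.
- **That the 80% power fails if both components are required.** At the planned recruitment, joint power is about 79–80%, so little is lost.

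Holm is also only one valid choice. Requiring both components needs no adjustment.

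**Conclusion.** The point holds as an undefined success rule, not as a demonstrated inflation. Two components share one main hypothesis, each was sized at an unsplit two-sided 5%, each is modelled separately, and nothing says how they combine. If either suffices, the two-sided family-wise error is up to 9.75%, about 7% to 9.75% for assumed correlations of 0.9 to 0, and false benefit alone is up to about 4.9% against 2.5%. If both are required, error is at most 5% and joint power at 392 recruited is about 79–80%, for assumed correlations of 0 to 0.3 and the article's own drop-out, SD and intraclass correlation. The rule should be fixed before the data are analysed.

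**What to change.** In the Sample size and Intention-to-treat sample sections:

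1. State that the main hypothesis is tested on the two 12-month contrasts only, by the Holm procedure at an overall two-sided 5%. Alternatively, state that both contrasts must be significant at two-sided 5%, and give the joint power of about 79–80%.
2. Treat the 15-month contrasts as secondary estimates of a sustained effect, outside the overall 5%. Interpret each only if its own component succeeded at 12 months, and at a stated level carried by that component. Under Holm this could be its initial 2.5% share; two such tests have a combined error of at most 5%.
3. If Holm is chosen, restate power at 392 recruited with 56% retained: about 83% for the mental and 93% for the physical component if both effects are real, and about 76% for the mental component if the physical has no effect.

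The cost is wording, with no added patients. Against 84.1% unadjusted, Holm costs the mental component about 1 point of power if both effects are real and up to about 8 points if the physical component shows none. Sizing each component at 2.5% instead would need 256 and 184 patients before drop-out, which Holm avoids at that price.
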